### Outcomes

4.6

#### Primary outcome measures

4.6.1

Real-time leakage will be measured by portable aerosol spectrometers (Grimm Model 1.109-006 and 007; Grimm Technologies, Ainring, Germany) during two selected clinical procedures. They will provide rapid measurement of particle concentration with optical sizes of 0.25–0.32 μm and different sizes from 31 channels. The system will consist of two spectrometers, the first will measure ambient air particle concentration, and the second will measure air particle concentration inside the respirator. This device will be placed on a designated table throughout the assessment. Participants will perform real-time measurements for real-time leakage at an average of 30 s intervals while performing the standard clinical procedures. A total of eight sets of data are collected within a 4 min procedure while 4 sets of data are collected in a 2-min one. Portable aerosol spectrometers have been used to measure real-time leakage during aerosol-generating procedures and some nursing procedures, namely, open suctioning, nasogastric-tube insertion, and napkin change (15, 16).

#### Secondary outcome measures

4.6.2

Fit rate and mask usability will be assessed and measured.

Quantitative fit testing will be conducted with a PortaCount respirator fit-tester system (model Pro+8038/8040; TSI limited), a recognized technology for counting air particles. The overall fit factor (range = 0–200) is the ratio of the concentration of a challenge agent (ambient particles) outside the respirator to the concentration of the same agent that leaks into the respirator (26). Fit rate is the proportion of the number of fit factor > 100 among total tested samples with a given respirator. A fit exceeding 100 indicates a passing rate, meaning that a given respirator is well-fitted to the wearer (3, 4, 12, 16, 27) (Figure 4).

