## Research hypothesis

3

We hypothesize that there is no significant group difference in real-time leakage between the use of traditional and new N95 respirators among Chinese healthcare workers during two clinical procedures (i.e., nasopharyngeal suctioning and CPR). We also hypothesize that the fit rate and mask usability have no significant difference between traditional and new N95 respirators among Chinese healthcare workers.

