### Trial design

3.1

The study is a randomized controlled, exploratory crossover trial with two arms (*n* = 100 in each arm) to examine and compare the real-time leakage of traditional and new respirators during two standard clinical procedures (i.e., nasopharyngeal suctioning and CPR).

The study will employ two sequential phases. A cross-sectional exploratory design in phase 1 will investigate the fit rate and usability of three types of respirators (two traditional melt-blown respirators with head-loop design and one new nano-respirator with ear-loop and clips) among Chinese HCWs, which is used to identify potential participants for the next phase. A cross-sectional design is appropriate to estimate the prevalence of unfit respirators through testing in a group of large samples.

Phase 2 is a randomized controlled crossover trial with two arms: participants donned with traditional best-fit respirators (either 1860S or 1870+), and participants donned with a new respirator (made of nanomaterial and ear-loop with clip design). A best-fit respirator refers to a given respirator obtaining the highest fit factor when donned by a user. A crossover design has advantages over a parallel experiment because the participating subject will act as his or her control, and possible incomparability between “intervention” and “control groups” could be eliminated. A two-arm study can yield reliable evidence about the effectiveness of real-time protection between traditional and new respirators. Randomization is performed as block randomization with a 1:1 allocation. To protect participants’ rights, anonymity, and confidentiality, the study was designed with the ethical principles of the Declaration of Helsinki. The paper complies with the SPIRIT recommendation for study protocol (25). The overall CONSORT flowchart of the study design is shown in Figure 1.

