### Who will take informed consent?

4.3

A research assistant will introduce the trial to the participants by demonstration. Participants will also receive an information sheet. The participants are screened with reference to the inclusion criteria, and eligible participants are invited to join the study using a signed written consent with an explanation. The research assistant will then collect the data of fit testing and mask usability results of all three respirators (two traditional respirators and one new respirator), gender, age, and body weight, which are records required for fit testing. Participants who pass one traditional respirator and one new respirator are invited to the phase 2 study.

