### Sample size

4.7

Calculation of sample size in this study was carried out based on Cochran’s formula for sampling size estimation (*N* = Z^2^p(1–p)/d^2^) (28, 29), where Z is 1.96 for a 95% confidence level, p is 40% for the estimated prevalence of unfit respirators (3, 4, 14), and d is 3% for an acceptable margin of error, for determining fit rate and mask usability (29). A quota sampling will be conducted to ensure that the samples include a certain proportion of students and staff (ratio of 1:2). Our previous study indicated that the medium to large effect size on group differences between traditional and new respirators can be obtained using real-time leakage (11). We will assume an effect of 0.40 to achieve a power of 80% at a 5% significance level (30). 1040 HCWs were recruited in phase 1, of which 60% of Chinese HCWs obtained a pass rate of fit testing in either traditional respirators (3, 4, 12, 14). Coupled with those who passed the fit testing for the new respirator (about 79%) as well as the 20% attrition rate, we have sufficient eligible samples to invite for the phase 2 study (1040 × 60% × 78% × 0.8 = 389). A total sample size of 200 will be required for this study.

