### Statistical methods for primary and secondary outcomes

6.1

Statistical Package for the Social Sciences (SPSS) version 27 will be used to perform descriptive and inferential statistical analysis. Descriptive statistics, including mean, standard deviation, percentage, and frequency, will be used to report the demographics, fit rate, and mask usability. The intention-to-treat (ITT) principle will be applied. We expect no carry-over and no period effect for this study based on previous experience. Chi-square test for categorical variables and independent sample t-test for continuous variables will be used to examine comparability among groups by randomization. Independent sample *t*-tests and paired *t*-tests will be used to compare real-time leakage among different groups of tested respirators during procedure, before and after procedures, respectively. Generalized estimating equations (GEE) will be used to evaluate the total real-time leakage difference in the interaction of time and cycles of chest compression. All the tests will be two-sided, and a *p*-value will be set at 0.05 for statistical significance.

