If the new N95 respirators have a better fit rate, greater mask usability, and less real-time leakage, increasing the production of respirators for Chinese HCWs to replace all traditional models is worthy of consideration. Our findings will also provide vital insight to encourage local manufacturers to develop more N95 respirators.

Some limitations deserve discussion. Firstly, this trial does not include all available N95 respirators in the market. The focus of this trial is not to promote some respirators better than others. Instead, the risk of real-time leakage of the use of N95 respirators should be verified for the specific design (e.g., ear-loop with clips) or shape (e.g., vertical flat-fold). Secondly, this trial does not include all aerosol-generating procedures in clinical settings but two common procedures are selected to simulate a range of intensity of physical activity. Hence, the results were impossible to generalize to all aerosol-generating procedures. Lastly, the current experiment is conducted through standard scenarios in a controlled simulation environment with mannequins. It is anticipated that the results of real-time leakage may be underestimated or regarded as minimal because the on-site clinical situations in resuscitation consist of many uncontrolled factors and different involved personnel.

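### A fit rate defined one respirator at a time cannot by itself support replacing all traditional models, because staff now have access to more than one

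*Protocol article*

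**What the plan says.** Phase 1 covers three respirators, "two traditional melt-blown respirators with head-loop design and one new nano-respirator with ear-loop and clips" (section 3.1). The research assistant will "collect the data of fit testing and mask usability results of all three respirators (two traditional respirators and one new respirator") for each participant (section 4.3), so every worker contributes three results.

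Section 4.6.2 fixes the outcome: "Fit rate is the proportion of the number of fit factor > 100 among total tested samples with a given respirator". Section 3 hypothesises that "the fit rate and mask usability have no significant difference between traditional and new N95 respirators among Chinese healthcare workers". Section 6.1 says descriptive statistics "will be used to report the demographics, fit rate, and mask usability".

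For the phase 2 arm, the traditional respirator is chosen per person: "A best-fit respirator refers to a given respirator obtaining the highest fit factor when donned by a user" (section 3.1). Section 4.2.1 requires a pass on that model and on the new one.

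The sample size section takes 40% as the prevalence of unfit respirators, then states that "60% of Chinese HCWs obtained a pass rate of fit testing in either traditional respirators".

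The Discussion says the fit-rate result will show which type suits most Chinese workers, and that a better new respirator would reduce the number of kinds in use. It continues: "If the new N95 respirators have a better fit rate, greater mask usability, and less real-time leakage", then replacing all the traditional models deserves consideration. Section 1.1 says hospitals regularly supply two to three major types.

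**The concern.** The outcome and the conclusion answer different questions. A per-model rate answers: if only this model were stocked, what share of workers would it fit? Replacing all traditional models raises another: how many workers fitted by some traditional model would the new one fail to fit, and how many would it gain?

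A worker who fails 1860S may pass 1870+, and the per-model rates do not count that second chance. Phase 2 cannot recover it, because its entrants have already passed both a traditional model and the new one. A purchasing body could therefore see a large lead over each traditional model although the gain in workers fitted is much smaller, absent or negative. The article presents this result as a reference for purchasing policy.

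**Working it through.** **The plan's own figures.** Cochran's formula gives 1.96² × 0.40 × 0.60 / 0.03² = 1024.4, so 1025, against 1040 recruited. The eligible pool is 1040 × 0.60 × 0.78 × 0.80 = 389.4, against the stated 389. Both reproduce.

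**Inputs.** Traditional models at 60% each and the new one at about 79% (section 4.7), with n = 1040 tested on all three. Section 1.1 gives local rates of 57.4–65.0% and 55–69%, used below for sensitivity. The overlap between models is not given, so it is an assumption shown as a range.

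**Share passing at least one.** With single-model rates a and b and a share o passing both, it equals a + b − o. Since o cannot exceed the smaller rate, the result is never below the larger one. At 60/60 it lies between 60% (the same people pass both) and 100%; under independence it is 1 − 0.40 × 0.40 = 84%.

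**Break-even.** At 60/60 the two-model provision equals 79% when o = 60 + 60 − 79 = 41%. As a correlation between the two pass/fail results, this is (0.41 − 0.36) / 0.24 = 0.21. On the latent normal scale used below it is r of about 0.33.

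**Range over overlap.** Assume a latent normal variable for each model, with a common correlation r across all three. Let u be the share passing the new model only, and v the share failing the new model but passing a traditional one. The paired difference is d = u − v, with standard error √[(u + v − d²)/1040].

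| r | At least one traditional | New minus one model | New minus at least one (95% CI) | Fail new, pass a traditional |
|---|---|---|---|---|
| 0 | 84.0% | +19 | −5.0 (−8.3 to −1.7) | 17.6% |
| 0.3 | 79.4% | +19 | −0.4 (−3.5 to 2.7) | 13.5% |
| 0.5 | 76.1% | +19 | +2.9 (0.0 to 5.8) | 10.1% |
| 0.7 | 72.2% | +19 | +6.8 (4.1 to 9.4) | 6.2% |

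Example at r = 0: u = 12.6% and v = 17.6%, so d = −5.0 points and the standard error is √[(0.126 + 0.176 − 0.0025)/1040] = 0.017.

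**Sensitivity to the traditional rates**, new still 79%, r = 0, 0.3, 0.5, 0.7:
- 57.4% and 65.0%: −6.1, −1.6, +1.6, +5.3 points, against single-model leads of 79 − 57.4 = 21.6 and 79 − 65 = 14.
- 65% and 65%: −8.8, −4.5, −1.4, +2.3 points, against a single-model lead of 14.

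The break-even r runs from about 0.18 (both at 57.4%) to about 0.58 (both at 65%).

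**The 60% in section 4.7.** If it is a single-model rate, it is only a lower bound for passing either model. If it is an at-least-one rate, neither model can exceed 60%, and the new respirator leads by 19 points at planning values with no reversal. The wording allows both readings.

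**The case against.** The strongest case against has four parts.

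- **Nothing is wrong with the definition.** Fit rate by model is how the article reports earlier studies, and it answers which model fits most workers. Phase 1 is labelled exploratory, is sized for precision, and has descriptive statistics for fit rate. This stands. A reader might infer that the plan will declare a spuriously significant advantage; the documents plan no such deciding test in phase 1. Leaving a test or contrast to an analysis plan that is not shown is also no fault.
- **The hypothesis may refer to phase 2.** Fit rate is recorded again after the procedures, where the traditional arm is the best-fit model. That reading is open, so the hypothesis should not be tied to phase 1. It does not close the gap, because phase 2 excludes anyone who failed the new respirator or both traditional ones.
- **Replacement is conditional.** It also needs better usability and less leakage, is only to be considered, and the limitations disclaim promoting particular respirators. True, but fit rate remains one of the three conditions, and as defined it cannot measure the coverage lost.
- **The reversal depends on unknowns.** Both traditional models are tested on the same face after the same training, so independence is the least natural case. The 79% matches the 78.8% reported for a head-loop model after nursing procedures, not the ear-loop model under test. The 55–69% is for 1860S and 9210, and the models behind 57.4–65.0% are not named. All this stands and limits the claim.

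**Conclusion.** The per-model fit rate is sound as a description but does not support the statements about using fewer kinds or replacing all traditional models. Its lead over a single model overstates the gain in coverage unless everyone who passes the less-fitting traditional model also passes the other. At 60/60/79% the overstatement is about 12 points at r = 0.7 (72.2 − 60) and 24 points at r = 0 (84 − 60).

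A reader might go further and infer that the new respirator fits fewer workers than the traditional pair. The document does not show that. At 60/60 the direction reverses only below r of about 0.33; at 0.5 and above the new respirator leads. If the ear-loop model's true rate falls below both traditional rates, every contrast agrees and the issue disappears. Nor is the 60% in section 4.7 shown to be an error; it is ambiguous.

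This is a secondary outcome, but one aimed at purchasing policy, and the correction is nearly free, so it should be made.

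**What to change.** - Keep the per-model fit rates in section 4.6.2 as the descriptive outcome.
- In sections 4.6.2 and 6.1, add one within-person comparison from phase 1: new respirator passed versus at least one of 1860S or 1870+ passed, as a paired difference in proportions with a 95% confidence interval. Report beside it the share who fail the new respirator but pass a traditional one.
- Base any statement about replacing all traditional models, or stocking fewer kinds, on that comparison.
- State openly that it was specified after recruitment ended (31 May 2023, section 8.1). The article says results have not been disseminated, so it can still be fixed before reporting, but it cannot be presented as prespecified.
- In section 4.7, say whether 60% is a single-model rate, and so a lower bound for passing either, or an at-least-one rate.

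The cost is some wording and one extra cross-tabulation. No new data are needed, because all three fit tests are already collected on each participant. The downside is that the new respirator's advantage may look smaller than in the single-model figures.

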**Figure 4 fig4:**
[figure not shown]
Quantitative fit testing system, tubing connection, and respirator.

Mask usability will be measured by an 11-item Mask Usability Scale (MUS), which involves the wearer’s feedback on tolerated heat, breathability, tightness, interference on speaking, skin itchiness, mask displacement, discomfort on the ear lobe, duration of use, interference on working efficiency, mist over glasses, and overall level of comfort (unpublished data). The MUS is rated on a six-point Likert scale, where a lower score means better usability. We have developed this scale and preliminarily used it in our previous studies (11, 16). We have also validated this scale on 283 nursing students with satisfactory psychometric properties (Cronbach’s alpha = 0.81–0.87; 2-week test–retest reliability: intraclass correlation coefficient = 0.821–0.822).

### Sample size

4.7

Calculation of sample size in this study was carried out based on Cochran’s formula for sampling size estimation (*N* = Z^2^p(1–p)/d^2^) (28, 29), where Z is 1.96 for a 95% confidence level, p is 40% for the estimated prevalence of unfit respirators (3, 4, 14), and d is 3% for an acceptable margin of error, for determining fit rate and mask usability (29). A quota sampling will be conducted to ensure that the samples include a certain proportion of students and staff (ratio of 1:2). Our previous study indicated that the medium to large effect size on group differences between traditional and new respirators can be obtained using real-time leakage (11). We will assume an effect of 0.40 to achieve a power of 80% at a 5% significance level (30). 1040 HCWs were recruited in phase 1, of which 60% of Chinese HCWs obtained a pass rate of fit testing in either traditional respirators (3, 4, 12, 14). Coupled with those who passed the fit testing for the new respirator (about 79%) as well as the 20% attrition rate, we have sufficient eligible samples to invite for the phase 2 study (1040 × 60% × 78% × 0.8 = 389). A total sample size of 200 will be required for this study.

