Quantitative fit testing is a recognized method to determine whether a tight-fitting respirator fits a wearer. This method adopts an electronic device to measure the ratio of particular air particles inside and outside the breathing zone (when donned with a respirator), and the ratio (i.e., fit factor) reflects the degree of leakage (3–5). Therefore, fit rate (the overall passing rate of fit testing) would be the primary concern to determine the fit of an N95 respirator to a population. Studies on American and Canadian HCWs indicated that several brands and types of respirators developed in the West (e.g., 3 M 1870 and 1860) fit 90–100% (9, 10). However, local retrospective analysis reported the fit rate of two N95 respirators (i.e., 3 M 1860S and 9210) from 84 to 91 nursing staff working in intensive care units (12). The fit rate was as low as 55–69% only. Further local studies examined the fit rate of several commonly used N95 respirators among nursing students and reported a consistently low fit rate of 57.4–65.0% (3, 4). In contrast to the results of studies conducted in the West, the fit rates of respirators were lower when donned by Chinese people. These results may reveal that tight-fitting N95 respirators require a match between mask design and facial anthropometry of a given population (e.g., face length and width) (15). However, the fit rates of all newly adopted N95 respirators for Chinese HCWs are unclear, except for some of the preliminary findings indicating that locally developed respirators (i.e., NASK head-loop model) provide a better-fit rate (78.8%) after nursing procedures (11).

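### The total of 200 matches a two-independent-group calculation, so the stated 80% power at an effect of 0.40 does not describe the crossover, which is over-powered for that effect

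*Protocol article*

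**What the plan says.** The Sample size section (4.7) of the protocol article gives the phase 2 assumptions in one sentence: "We will assume an effect of 0.40 to achieve a power of 80% at a 5% significance level (30". It ends: "A total sample size of 200 will be required for this study". The statistical methods (6.1) add: "All the tests will be two-sided". No test, standard deviation or within-person correlation is attached to the 0.40.

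The Trial design section (3.1) describes the study thus: "The study is a randomized controlled, exploratory crossover trial with two arms", with 100 in each arm, and justifies the crossover on the ground that participants serve as their own controls. The Intervention description (4.5.2) has each participant rest for 10 minutes, put on the other respirator and repeat the leakage measurement. The arms are therefore sequences, and every participant contributes both respirators.

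For leakage, section 6.1 assigns independent-sample t-tests to the comparison during the procedure and paired t-tests to before versus after.

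On the source of the assumptions, 4.7 refers to the team's previous study (reference 11) for a medium to large effect on leakage. The Background attributes to that study a fit rate for a particular model: "i.e., NASK head-loop model) provide a better-fit rate (78.8%) after nursing procedures (11". In 4.7 the pool of eligible people uses "those who passed the fit testing for the new respirator (about 79"%, entered as 78% in the product. The new respirator in this trial is the ear-loop model with clips.

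**The concern.** A two-group formula ignores the fact that each participant supplies both measurements. If 200 came from such a formula, the stated 80% belongs to a trial with 100 people on each respirator and no crossover.

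What is at stake is interpretation. A reader told that the trial had 80% power for 0.40 will take 0.40 as roughly the smallest difference it could detect reliably. If the real figure is clearly smaller, a significant result may reflect a smaller leakage difference than the reader supposes. That matters here because the Discussion considers replacing the traditional models if the new respirator performs better.

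**Working it through.** **Inputs.** Effect 0.40, power 80%, alpha 5%, total 200 (4.7); two-sided tests (6.1); 100 per arm (3.1); both respirators worn by every participant (3.1 and 4.5.2). Assumptions not in the article: 0.40 is a standardised mean difference d on the between-person SD, each person supplies one leakage summary per respirator, and rho is the within-person correlation between the two, shown over a range.

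**Step 1: reproduce 200.** For two independent groups, n per group = 2(z₀.₉₇₅ + z₀.₈₀)²/d² = 2(1.960 + 0.842)²/0.40² = 98.1, so 99 per group and 198 in total. The t-based solution is 99.08, so 100 per group and **200** in total. Power at 100 versus 100 is 80.4% (t) or 80.7% (normal). The stated figure is reproduced.

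**Step 2: do other usual readings give 200?**

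| Reading | Participants needed |
|---|---|
| One-sided, two groups | 2 × 78 = 156 |
| Paired t-test, 0.40 as standardised paired difference | 52 |
| 0.40 as Cohen's f (d = 0.8), two groups | 2 × 26 = 52 |
| Two-group number inflated for 20% attrition | 198/0.8 → 248, or 200/0.8 = 250 |

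None does.

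**Step 3: power of the crossover at d = 0.40.** The standardised paired difference is d_z = d/√(2(1 − rho)), tested by a paired t-test.

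| rho | d_z | Power, 200 pairs | Power, 160 pairs | Participants for 80% |
|---|---|---|---|---|
| 0 | 0.283 | 97.8% | 94.5% | 101 |
| 0.3 | 0.338 | 99.7% | 98.9% | 71 |
| 0.5 | 0.400 | 99.99% | 99.9% | 52 |
| 0.7 | 0.516 | >99.99% | >99.9% | 32 |

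The 160 is 200 × 0.8, using the article's 20% attrition rate. With 200 pairs, power falls to 80.4% only at rho = −1. If 0.40 was already meant as d_z, power with 200 pairs is 99.99%. Even an unpaired test of all 200 against all 200 measurements has a nominal power of 97.9%.

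**Step 4: effect detectable with 80% power.** For 200 pairs, d_z = 0.199. Converting with d = d_z√(2(1 − rho)):

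- rho = 0: 0.199 × 1.414 = 0.28
- rho = 0.5: 0.199 × 1 = 0.20
- rho = 0.7: 0.199 × 0.775 = 0.15

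For 160 pairs, d_z = 0.223.

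**Step 5: the eligible pool.** 1040 × 0.60 × 0.78 × 0.8 = 389.4, as printed; with the 79% in the text it is 394.4. The pass rate enters this product only and plays no part in the 200.

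**The case against.** The best defence is that 6.1 names an independent-sample t-test for leakage during the procedure, which is the primary outcome, and that 100 per arm suits it. If that test compared first-period data only, 100 versus 100, the 80% would be right. But the article nowhere restricts the comparison to the first period, and doing so would discard the within-person control that it gives as its reason for a crossover. What stands is that 6.1 and 4.7 have to be reconciled together.

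A second defence is that sizing a crossover by the two-group formula is merely conservative when no within-person correlation is known. That is fair as to consequence: the 80% target is met and exceeded. It does not make 80% the correct description of the design.

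Three stronger readings are tempting and are not supported:

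- *The detectable difference is half the one stated.* This sets a d_z of 0.20 beside a d of 0.40. On the between-person scale the detectable d is 0.28 at rho = 0, which is 70% of 0.40, and is half only at rho = 0.5.
- *The 200 rests on data from another respirator.* The 0.40 is stated as an assumption, motivated by the previous study rather than quoted from it. The 79% feeds only the 389. It carries no citation, and its link to that study is inferred from its closeness to 78.8%.
- *There may be too few eligible people.* The article gives no observed pass rate for the ear-loop model from which to show this, and Trial status (8.1) says that recruitment is complete.

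**Conclusion.** The point holds as a misdescription of power. The total of 200 matches the two-independent-group number, and the stated 80% is not the power of the crossover described. At d = 0.40 on the between-person SD, 200 pairs give at least 97.8% for any rho of 0 or more, and 160 pairs at least 94.5%. The conclusion does not depend on the particular rho, since 200 pairs exceed the two-group power for every value above −1.

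It rests on reading 0.40 as a standardised mean difference and on inferring the formula from the match. The direction is over-powering, so neither the validity nor the adequacy of the primary comparison is threatened.

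A secondary caution: the Background describes the study behind the effect assumption as concerning the head-loop model, while this trial tests the ear-loop model. That calls for a sentence of disclosure and does not refute the 200.

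**What to change.** Reword 4.7 along these lines, and carry the statement into the results report:

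> The total of 200 was derived for two independent groups of 100 at a standardised difference of 0.40 (two-sided 5%, 80% power). In the crossover, 200 participants give 80% power for a standardised paired difference (d_z) of 0.20. This equals a between-person standardised difference of 0.28, 0.20 or 0.15 if the within-person correlation is 0, 0.5 or 0.7. With 160 completers the detectable d_z is 0.22.

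The investigators should confirm the two-group derivation before adopting the first sentence. Base the statement on the paired traditional-versus-new comparison, and amend 6.1 so that the test named for leakage during the procedure agrees with it.

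Add one sentence saying that the effect assumption was motivated by a study that the Background describes as concerning the head-loop model. State the source of the 79% and settle 79% against 78%. Replace the forecast 389 with the observed phase 1 count of people who passed both a traditional respirator and the ear-loop model.

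The cost is a few sentences and one count from data already collected. Enrolment does not change.
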